# Effects of recombinant human erythropoietin on cognition and neural activity in remitted patients with mood disorders and first-degree relatives of patients with psychiatric disorders: a study protocol for a randomized controlled trial

**DOI:** 10.1186/s13063-018-2995-7

**Published:** 2018-11-06

**Keywords:** Bipolar disorder, Depression, Cognition, Cognitive dysfunction, Erythropoietin, Pro-cognitive efficacy, Prefrontal cortex, Functional magnetic resonance imaging, Biomarker

## Abstract

**Background:**

Bipolar disorder (BD) and unipolar disorder (UD) are associated with cognitive deficits and abnormal neural activity in a “cognitive control network.” There is an increased prevalence of cognitive dysfunction in psychiatric patients’ first-degree relatives, which constitutes a risk factor for psychiatric illness onset. However, there is no treatment with enduring pro-cognitive efficacy. We found preliminary evidence for beneficial effects of eight weekly doses of recombinant human erythropoietin (EPO) on cognition in BD in a recent randomized controlled trial (RCT). The present RCT consists of two sub-studies that extend our previous work by investigating important novel aspects: (1) the effects of 12 weekly doses of EPO on cognition in first-degree relatives of patients with BD, UD, or schizophrenia; and (2) the effects of extending the treatment schedule from 8 to 12 weeks in remitted patients with BD or UD; and (3) assessment of early treatment-associated neural activity changes that may predict cognitive improvement.

**Methods:**

The trial comprises two parallel sub-studies with randomized, controlled, double-blinded, parallel group designs. First-degree relatives (sub-study 1; *n* = 52) and partially or fully remitted patients with BD or UD (sub-study 2; *n* = 52) with objectively verified cognitive dysfunction are randomized to receive weekly high-dose EPO (40,000 IU/mL) or placebo (saline) infusions for 12 weeks. Assessments of cognition and mood are conducted at baseline, after two weeks of treatment, after treatment completion, and at six-month follow-up. Functional magnetic resonance imaging (fMRI) is conducted at baseline and after two weeks of treatment. Psychosocial function is assessed at baseline, after treatment completion and six-month follow-up. The primary outcome is change in a cognitive composite score of attention, verbal memory, and executive functions. Statistical power of ≥ 80% is reached to detect a clinically relevant between-group difference by including 52 first-degree relatives and 52 patients with BD or UD, respectively. Behavioral data are analyzed with an intention-to-treat approach using mixed models. fMRI data are analyzed with the FMRIB Software Library.

**Discussion:**

If this trial reveals pro-cognitive effects of EPO, this may influence future treatment of mood disorders and/or preventive strategies in at-risk populations. The fMRI analyses may unravel key neurobiological targets for pro-cognitive treatment.

**Trial registration:**

ClinicalTrials.gov, NCT03315897. Registered on 20 October 2017.

**Electronic supplementary material:**

The online version of this article (10.1186/s13063-018-2995-7) contains supplementary material, which is available to authorized users.

## Background

Cognitive deficits occur in moderate to severe degree in patients with bipolar disorder (BD) and unipolar disorder (UD) [1–6]. These deficits are not only present during acute episodes, but commonly persist after remission [1–7]. This negatively affects patients’ quality of life, recovery rates, and socio-occupational functioning [6, 8–12] of which reduced work capacity is the largest area of socioeconomic burden [13, 14]. A higher occurrence of mild to moderate deficits has also been detected in BD, UD, and schizophrenia patients’ unaffected first-degree relatives compared with healthy controls with no first-degree family history of psychiatric disorder [15–19]. These impairments increase the risk of psychiatric illness onset in these individuals [20]. Cognition is therefore a key treatment priority in patients with mood disorders and genetically predisposed individuals [21]. Nevertheless, there are no existing treatments with solid and enduring efficacy on cognitive dysfunction in these populations. New candidate treatments have only produced disappointing or preliminary results [22]. This is partially related to major methodological challenges, including the absence of a sensitive brain-based biomarker model to detect the efficacy of candidate treatments in phase 1 and 2 clinical trials [23]. In fact, candidate drug treatment screening typically relies on animal models with compounds being directly moved into large-scale, costly clinical efficacy trials, in cases of beneficial effects in the animal model. However, detection of pro-cognitive efficacy in animal models has poor predictive value in clinical trials [24], which underlines the need for a more valid, sensitive biomarker model for pro-cognitive efficacy. Emerging evidence highlights blood-oxygen-level dependent (BOLD) functional magnetic resonance imaging (fMRI) response in the prefrontal cortex (PFC) as a promising biomarker for cognitive dysfunction and early cognitive improvement. In particular, aberrant (primarily hypo-) activity in the dorsolateral and medial PFC (dlPFC and mPFC) during working memory and episodic encoding tasks is the most reproducible neural marker of cognitive dysfunction across neuropsychiatric disorders, including BD, UD, schizophrenia, and genetically predisposed individuals [25–31]. This aberrant activity reflects difficulties with selecting and maintaining stimuli in working memory and strategic memory encoding [32]. Reversal of aberrant dorsal prefrontal activity may therefore constitute a promising neural biomarker for cognitive improvement.

Preclinical and clinical studies point to erythropoietin (EPO) as one of the most promising candidate cognitive enhancement treatments [33]. EPO is produced in the brain where it exerts neurotrophic and neuroprotective actions and plays a central role in cognitive functioning [33–37]. Clinical studies have found that repeated systematically administered high-dose recombinant human EPO versus placebo (saline) improves attention, memory, and executive functions after 8–12 weeks of treatment across neuropsychiatric disorders, including multiple sclerosis, Parkinson’s disease, schizophrenia, treatment-resistant depression (TRD; defined as failure to respond to ≥ 2 different types of antidepressant treatments given in sufficient doses over sufficient time [38]), and BD [39–43]. In particular, two randomized placebo-controlled trials from our group revealed that eight weekly EPO infusions improved several cognitive domains in patients with BD and TRD [39, 40]. This was accompanied by increased activity in dlPFC and dorsomedial PFC (dmPFC) during working memory and episodic encoding tasks [44, 45]. Notably, a single dose of EPO enhances cognition-related dlPFC and dmPFC activity without producing any change in red blood cells [46, 47]. This suggests that the EPO-associated increase in task-related dorsal PFC (dPFC) reflects direct effects of EPO in the brain. Taken together, these preliminary findings point to EPO as a promising cognition treatment and to neuronal activity change in the dPFC as a key neural correlate of treatment-related improvement of cognition. Nevertheless, our EPO trial had a number of methodological limitations [39, 40]. First, cognitive dysfunction was not verified with an objective (i.e. neuropsychological) measure before enrollment of participants. This is problematic since we found in post-hoc analyses that objective cognitive impairment at baseline was the strongest predictor of treatment success on cognition [48, 49]. Second, the primary outcome was a single measure of verbal memory, which contrasts with the recently published recommendations by the International Society for Bipolar Disorders (ISBD) Targeting Cognition Task Force that the primary outcome in cognition trials should be a broad cognitive composite score spanning attention, memory, and executive function [50]. Third, the lack of long-term follow-up assessment hampered insight into whether treatment-associated cognitive improvement was long-lasting. Fourth, we had not assessed functional capacity in the patient sample and thus had no insight into whether the EPO-related improvement of cognition translated into better functional capacity.

### Aims and hypotheses

The aims of the present EPO trial are threefold. First, we aim to investigate whether 12 weekly recombinant human EPO infusions ameliorate cognitive impairments in first-degree relatives without psychotic or mood disorders to patients with BD, recurrent UD, or schizophrenia (sub-study 1). This will allow for the first time to judge the disease-independent response of inherent cognitive genetic traits. Second, we will examine whether a longer treatment period is associated with similar or stronger cognitive improvement in remitted patients with BD or recurrent UD (defined as ≥ 2 treatment-requiring depressive episodes) (sub-study 2). Third, we will explore with fMRI the early neuronal changes that are predictive of subsequent clinically relevant cognitive improvement across these groups. We hypothesize that:12 weekly EPO infusions improve cognition in first-degree relatives and remitted patients with BD or recurrent UD in comparison with saline.EPO versus saline-treated participants will display early cognition-related neural activity in dorsal PFC in the direction of the activity in healthy controls, which will correlate with cognitive improvement.

## Methods and design

### Participants

We will recruit 52–58 first-degree relatives without psychotic or mood disorders to patients with BD, recurrent UD, or schizophrenia (sub-study 1) and 52–58 patients with BD or recurrent UD in partial or full remission (defined as a score of ≤ 14 on the Hamilton Depression Rating Scale 17-items (HDRS-17; [51]) and the Young Mania Rating Scale (YMRS; [52]) (sub-study 2) with objectively verified cognitive dysfunction to obtain a complete dataset for 52 participants per sub-study (assuming a 10% drop-out rate from inclusion to treatment completion). Participants will be recruited from psychiatric centers in The Mental Health Services in the Capital Region of Denmark, consultant psychiatrists in the Capital Region of Denmark, as well as through advertisements on relevant websites. Within each sub-study, half of the participants will be randomized to receive active treatment (*n* = 26–29), while the other half will receive placebo (*n* = 26–29).

Eligible participants are aged 18–65 years, have fluent Danish skills, and display objectively verified cognitive dysfunction according to the Screen for Cognitive Impairment in Psychiatry (SCIP) [53–55]. Specifically, participants must have a total SCIP score of ≤ 77, which provides adequate sensitivity and specificity for cognitive impairment (86% and 70%, respectively) [53], or have a score corresponding to ≥ 1 standard deviation (SD) below the norm on ≥ 2 SCIP subtests [50, 53]. For individuals with a verbal IQ ≥ 120 (i.e. ≥ 1 SD higher than the average IQ in age-matched healthy control participants) according to the Danish Adult Reading Test (DART [56]), the adjusted inclusion criterion is a score > 1 SD below the norm on ≥ 1 SCIP subtest. In this way, cognitive impairment is to some degree established with reference to participants’ premorbid IQ in accordance with recent guidelines by the ISBD Targeting Cognition Task Force [50].

Patients are eligible if an ICD-10 diagnosis of BD or recurrent UD is confirmed with the Schedules for Clinical Assessment in Neuropsychiatry (SCAN) [57]. The maximum daily use of benzodiazepines allowed is 22.5 mg oxazepam (benzodiazepines will be avoided on the day of neuropsychological assessments). Patients’ medication must remain unchanged during the study period, unless a change of medication is deemed necessary by their treating psychiatrist. First-degree relatives are allowed to have minor psychiatric disorders (defined as ICD-10 codes > F40), since these individuals are at particular risk of (major) psychiatric illness onset. Specifically, first-degree relatives are eligible even if diagnosed with a psychiatric disorder categorized within the ICD-10 as F40–49 (anxiety, dissociative, stress-related, somatoform, and other non-psychotic mental disorders), F50–59 (behavioral syndromes associated with physiological disturbances and physical factors), and F60–69 (disorders of adult personality and behavior) codes, as long as these disorders only influence their current state to a minor degree (i.e. they are well-treated at the time of inclusion).

Exclusion criteria for both sub-studies are individuals with intellectual disability (defined as an estimated IQ < 70) [50], schizophrenia or schizoaffective disorder, neurological disorder (including dementia), current alcohol or substance abuse (up to 3 months prior to inclusion), or history of head trauma. To ensure safety of EPO treatment throughout the study, candidates are also excluded if they have significant medical conditions (e.g. heart disease, diabetes, renal failure, untreated/insufficiently treated hypertension, malignancies, and/or thromboses), personal or first-degree family history of epilepsy or thromboembolic events, have received electroconvulsive therapy (ECT) three months before participation, are dyslexic, use contraceptive medications, smoke, are pregnant, or are breastfeeding. Regarding fMRI assessments, participants are not eligible if they suffer from claustrophobia or have a pacemaker and/or other metal implants inside their bodies. Participants, who do not meet these fMRI inclusion criteria will not be excluded from the trial per se, but only from the two fMRI assessments.

These criteria are similar to the procedures in our previous studies [39, 40, 58]. To ensure that participants receive a sufficient concentration of EPO, candidates are excluded if they weigh < 45 or > 95 kg or are overweight (BMI > 30). Participants must be able to provide written informed consent to be included in the study. These procedures are in accordance with the ethical standards of the Danish Research Ethics Committee for the Capital Region of Denmark (protocol number H-16043370) and The Danish Data Protection Agency Capital Region of Denmark (protocol number RHP-2017-020). See Additional file 1 (SPIRIT 2013 Checklist) for a trial protocol checklist.

### Setting

Participants will receive intravenous infusions of either recombinant human EPO (Epoetin alpha; Eprex; 40,000 IU/mL) or placebo (1 mL NaCl) diluted with 100 mL saline (0.9% NaCl) administered for 15 min once a week (7 ± 2 days) during a 12-week study period at the Copenhagen Affective Disorder Research Center (CADIC), Psychiatric Centre Copenhagen, Rigshospitalet. The EPO doses are similar to those found to be effective for modulating neural and cognitive function with short-term administration [46] and for enhancing cognition with long-term treatment [39, 40, 42, 59]. Outcome assessments are also carried out at Psychiatric Centre Copenhagen and Neurobiology Research Unit (NRU), Rigshospitalet.

### Study design and procedures

The trial has a randomized, double-blinded, placebo-controlled, parallel group design. The study design comprises four major assessments (baseline, week 3, week 13, and a six-month follow-up after treatment completion) and weekly safety monitoring and study medication infusions during the 12-week treatment period. Participants will be informed about the study and given a participant information sheet. Before undergoing eligibility assessments, participants provide written informed consent, which will be obtained by one of the named authors.

The baseline assessment is divided into two days, 1–3 days apart for practical reasons and to avoid attrition. On the first day of the baseline assessment, participants are mood rated with the HDRS-17 and YMRS to ensure remission and afterwards complete an fMRI scan at Copenhagen University Hospital, Rigshospitalet. On the second baseline day, participants attend Psychiatric Centre Copenhagen for a fasting research blood test (peripheral biomarker measure) followed by an assessment of cognitive functions with a neuropsychological test battery, verbal IQ (assessed with the Danish Adult Reading Test; DART [56]), and filling in questionnaires concerning subjective cognitive complaints, quality of life, level of functioning, and functional capacity, as well as depression and mania symptom severity ratings. Functional capacity will be assessed using a clinician-rated interview and a performance-based task. Mood ratings are performed with the HDRS-17 [51] and the YMRS [52]. After two weeks of treatment (i.e. two doses of EPO or saline), fMRI scan, research blood samples, neuropsychological testing, mood ratings, and questionnaires on subjective cognitive difficulties are repeated. After treatment completion (week 13) and at the six-month follow-up, the neuropsychological tests, questionnaires concerning subjective cognitive complaints, quality of life, and functional capacity (self-reported and performance-based) are repeated. Research blood samples are collected in week 13, but not at the six-month follow-up. Sleep quantity and quality in the past three days is assessed before each of the four major assessment time points and with online self-rating using the Pittsburgh Sleep Quality Inventory (PSQI) [60] assessing sleep quality one week before the baseline, week 3, week 13, and the six-month follow-up assessment. Blood samples are collected at baseline and weeks 3 and 13 for assessment of potential blood-based biomarkers of pro-cognitive effects. An intermediate mood symptom rating for patients (sub-study 2) is performed at week 7 to assess whether they are in (partial) remission throughout the study period. To ensure safety, we conduct weekly monitoring, comprising thorough medical examinations and blood test evaluations, for the duration of the treatment course and in weeks 13 and 15. Pregnancy tests are mandatory for and will be performed on fertile female participants before the first study medication infusions and every second week during the active treatment period. Blood screening and thorough medical examinations are undertaken at baseline, weekly throughout the 12-week treatment period as well as one and three weeks after treatment completion to continuously monitor red blood cell levels and ensure participant safety.

EPO will be kept at 2–8 °C during transport and storage to reduce the risk of damaging the medication and potential related adverse side effects. EPO will be dissolved in 100 mL saline and infusions will be given intravenously over 15 min to reduce the possibility of acute allergic reactions. If blood test analyses reveal significantly increased hematocrit (men: > 50%; women: > 48%) at two consecutive measurements within the same week, bloodletting (450 mL) will be performed on a weekly basis with no cessation of treatment before hematocrit values are normalized. Patients are therefore asked to regularly drink plenty of water to avoid “pseudo”-increases in hematocrit. In cases of significant increase in thrombocytes (> 400 billion/L) or drop in reticulocytes (ERC(B) < 1 × 10^− 3^), two repeated controls will be performed in the following week. If thrombocyte and/or reticulocyte values remain abnormal, participants will be withdrawn from further study participation and monitored with weekly medical examinations and blood samples until values are stabilized. If necessary, these participants will be hospitalized for observation. Lists of any pseudo-anonymized outcome data collected for participants who discontinue or deviate from further study participation will be kept in a locked cabinet.

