#### Primary, secondary, and tertiary outcome measure analyses

Behavioral data from neuropsychological test score performance, subjective cognitive impairments, quality of life, level of functioning, psychosocial functioning, and mood symptoms (i.e. data from the primary, secondary, and tertiary outcomes) will be analyzed using mixed models design and intention-to-treat (ITT) analyses in cases of missing data. Data will be analyzed for every participant with any assessment. No interim analyses will be performed.

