#### Sample size and power calculation

Sample size and statistical power has been calculated by PharmaConsulting Group AB with Statistical Analysis Software (SAS), based on our previous findings assessing cognitive effects of weekly infused EPO [48]. The difference in cognitive change between the EPO and the saline-treated groups from baseline to after treatment was 0.5 SD [48]. In this trial, we estimate a clinically relevant differential change in the primary cognitive composite score between the EPO and placebo groups from baseline to week 13 (treatment completion) to be at least 0.4 SD (corresponding to a moderate effect size) with a SD of the mean change of 0.5 between these groups. This is consistent with the recommendations listed by the ISBD Cognition Task Force [50]. Specifically, the task force indicated that a differential change between groups of 0.2–0.4 SD on a global composite score reflects a potentially clinically relevant change, since this may translate into moderate–large functional improvement in patients with mood disorders [50]. In our eight-week EPO trial, the difference regarding change in the cognitive composite score from baseline to treatment completion was 0.5 SD between the EPO and the saline groups [48]. Based on the ISBD task force recommendations and our earlier findings regarding effects of longer-term EPO treatment, we estimate that a sample size of *N* = 104 (i.e. *n* = 52 participants within each sub-study with *n* = 26 in each treatment group) will reach a ≥ 80% power for detecting a similar clinically relevant differential change of 0.4 SD in the primary cognitive composite outcome measure with a SD of this change of 0.5 between the treatment groups at an alpha level of 5% (two-sided test). Based on our assumption of a 10% drop-out rate from baseline to treatment completion, we plan to recruit up to *n* = 58 for each sub-study to achieve complete datasets for *n* = 52 participants per sub-study (first-degree relatives and patients, respectively).

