### Safety procedures and monitoring of EPO infusions

EPO is a common treatment option for anemia patients and has a good safety profile when carefully monitored. However, hematopoietic effects of repeated EPO administration are associated with risk of hypertension and blood clotting [91]. Indeed, EPO has been associated with increased mortality in severely ill stroke patients with previous thromboembolic disease, including patients given thrombolytic treatment [92, 93]. To ensure participant safety in this trial, we therefore implement extensive exclusion criteria to exclude candidates at increased risk of thromboembolic events. Extremely rare but serious side effects associated with long-term EPO administration in patients with chronic severe somatic diseases are thromboses at the site of dialysis in patients with kidney failure, seizure, and potential tumor growth [94]. The rare condition, pure red cell aplasia (PRCA), has been detected with subcutaneous infusions and poor packaging of the EPO medication. However, its incidence rate has fallen to 0.3/100,000 patient years [95–97]. Reticulocyte counts constitute the first indicator of PRCA and are therefore thoroughly monitored. We observed no serious adverse events in eight weeks of weekly EPO infusions in the proposed dose and administration form in our previous studies of 84 patients with TRD or BD [39, 40]. EPO-related hematocrit levels increased to an extent that necessitated blood-letting in five (14%) of the 35 EPO-treated patients in weeks 3–8 (with one in week 3). This corresponds to observations by Ehrenreich et al. [41, 42]. We discontinued EPO treatment in six patients (17%) after 5–7 weeks due to thrombocyte level increase (these participants completed all assessments). Participant safety monitoring therefore involves thorough medical examinations, systolic and diastolic blood pressure measurement, blood sampling, electrocardiography (ECG), and additional safety parameters at baseline, weekly during the study, and at three weeks after EPO/placebo treatment completion. Due to careful adherence to the exclusion criteria and weekly safety monitoring, we evaluate the risk of such side effects and adverse events of EPO treatment to be extremely low in this trial. Further, participants will be informed of all potential adverse effects before randomization and are instructed that iron supplements (which increase hematocrit levels) are prohibited during the active treatment period. Although the risk of potential thrombosis or suspected PRCA is low, included participants are given a pocketsize plastic card with instructions about what to do and contact details to medical doctors at the local emergency department in case these symptoms appear. Participants stay at the clinic for observation for at least 30 min after each infusion for a research nurse to monitor potential acute side effects of EPO (e.g. rash at the infusion site or headache).

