
### Ethical considerations

We evaluate the risks and disadvantages of participating in the study to be minimal based on previous EPO trials [39, 40] and the described precautions, exclusion criteria, and carefully established treatment plan in case of side effects.

Although patients are not required to withdraw from their usual antidepressant or mood stabilizing medication, they are requested not to change their doses or treatment during the study course. This may give rise to ethical considerations for the included remitted patients, albeit we show consideration for their safety, rights, and wellbeing by excluding those who are required to change the type or dose of their mood stabilizing medical treatment by their psychiatrist. In case of significant symptom worsening, patients’ clinical needs, integrity, and autonomy come before the scientific interests of the study. Because of the lack of effective treatments targeting cognitive dysfunction in mood disorders [22, 98], the use of a placebo group is necessary for investigating potential beneficial cognitive effects of EPO. We are unable to offer active EPO treatment to these participants after trial completion given the only preliminary evidence for efficacy of EPO on cognition. This is likely to be disappointing for the 50% of participants randomized to saline. The duration of neuropsychological test assessments and mood ratings may lead to attrition in some participants. However, we keep the duration of neuropsychological assessments and fMRI scans to a minimum to avoid attrition and reduce the risk of drop-out. Albeit the procedure is safe and non-invasive, some participants may experience it as claustrophobic and anxiety provoking. For these reasons, we exclude people, who suffer from claustrophobia from fMRI assessments. Blood sampling may be associated with slight discomfort but is routine hospital care. Participants will benefit from the extra care and close contact with medical doctors, psychologists, and a research nurse during study participations, which has demonstrated beneficial effects [99]. Furthermore, the participation in the trial is considered beneficial for first-degree relatives to patients with BD, recurrent UD, or schizophrenia, since enrolment requires objectively verified cognitive dysfunction, which is known to increase psychiatric illness onset risk in these high-risk individuals [20]. All participants are reimbursed for their time and the transport expenses associated with taking part in the study.

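### The blood-value rule ends study participation, not only infusions, so as written it loses week-13 cognition for a treatment-linked reason, probably mainly in the EPO arm

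*Protocol article*

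**What the plan says.** Study design and procedures sets out what follows when repeat controls do not clear an abnormal blood value: "If thrombocyte and/or reticulocyte values remain abnormal, participants will be withdrawn from further study participation". The only later contact it names is medical follow-up with blood tests until the values settle, with admission if needed. It then says how lists of outcome data from people who discontinue will be stored. It does not say that cognitive testing goes on.

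Safety procedures and monitoring of EPO infusions describes the previous eight-week trial differently: "We discontinued EPO treatment in six patients (17%) after 5–7 weeks due to thrombocyte level increase (these participants completed all assessments").

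The analysis section plans mixed models with an intention-to-treat (ITT) approach to missing data, and adds: "Data will be analyzed for every participant with any assessment". Sample size and power calculation plans for 52 complete datasets per sub-study from up to 58 recruited: "Based on our assumption of a 10% drop-out rate from baseline to treatment completion". It mentions no extra allowance for the withdrawal rule.

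On a related matter, Participants asks that patients' medication stay unchanged "unless a change of medication is deemed necessary by their treating psychiatrist", and Limitations says medication will be recorded for post-hoc analysis. Ethical considerations instead speaks of protecting patients "by excluding those who are required to change the type or dose of their mood stabilizing medical treatment by their psychiatrist".

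**The concern.** An event that in the previous trial ended only the infusions now ends participation, and no reason is given. The previous cases arose in EPO-treated patients after 5 to 7 weeks, which in this trial falls after the week-3 assessment and before the week-13 primary endpoint. Their primary outcome would therefore be missing by rule, for a reason linked to the treatment, and probably mostly in one arm.

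An analysis plan cannot recover scores that were never collected. For those withdrawn, the mixed model would infer week 13 from their baseline and week-3 scores and from the course of EPO participants who stayed on treatment. That is closer to the effect of EPO in those who continue than to the effect in everyone randomised. If any benefit fades after stopping, the two differ, and nothing in the collected data would show it.

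**Working it through.** **Inputs.** From Sample size and power calculation: difference 0.4, SD of change 0.5, "at an alpha level of 5% (two-sided test"), 26 per arm, 10% drop-out, up to 58 recruited. From Participants: up to 29 per arm. From Safety procedures: six EPO patients stopped for thrombocytes, 35 EPO-treated. From Limitations and Study feasibility: one drop-out previously, 84 patients.

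**1. The plan's own figure.** The article claims at least "80% power for detecting a similar clinically relevant differential change of 0.4 SD". The two-sample t noncentrality is 0.4 / (0.5 × √(1/n₁ + 1/n₂)), with n₁ + n₂ − 2 degrees of freedom. At 26 and 26 it is 2.88, and power is 80.7% (82.2% by the normal approximation). Recruitment: 52 / 0.9 = 57.8, so 58. The stated figures reproduce. The allowance is 58 − 52 = 6 per sub-study, or 3 per arm.

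**2. Expected withdrawals.** 6/35 = 17.1%. With 29 EPO participants, 29 × 6/35 = 4.97. That is above the EPO arm's 3, but 4.97/58 = 8.6% of the sub-study, within the overall 10%. The chance that 4 or more of 29 are withdrawn at this rate is 76% (binomial). The exact 95% interval for 6/35 is 6.6% to 33.6%, or 1.9 to 9.8 of 29.

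**3. Power under the rule**, assuming no placebo withdrawals (expected numbers, so fractions are kept):

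| EPO withdrawal | Other loss, both arms | EPO / placebo complete | Total | t power |
|---|---|---|---|---|
| 17.1% | none | 24.0 / 29.0 | 53.0 | 81.2% |
| 17.1% | 1/84 (assumed) | 23.7 / 28.7 | 52.4 | 80.7% |
| 17.1% | 10% (assumed) | 21.6 / 26.1 | 47.7 | 76.8% |
| 24.6% (assumed) | none | 21.9 / 29.0 | 50.9 | 79.1% |
| 24.6% (assumed) | 10% (assumed) | 19.7 / 26.1 | 45.8 | 74.6% |

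The 24.6% assumes a constant hazard carried from 8 to 12 weeks: 1 − (1 − 6/35)^(12/8), or 7.1 of 29. The 1/84 takes all 84 patients as the denominator for the one earlier drop-out.

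**4. What the analysis sees.** A participant withdrawn after weeks 5 to 7 has baseline and week-3 scores, so is analysed. Week 13 and six months are absent. At the 17.1% rate, that is 17% missing in EPO against 0% in placebo (assumed), before any other loss.

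**The case against.** The strongest defence is that the article is condensed and its wording is loose. It mentions outcome data from people who discontinue, the team kept such patients in assessment before, and the full protocol may say so again. The storage sentence is indeed ambiguous, though it fits data already in hand at least as well. The rule itself is stated: participation ends and only safety contact follows. If continued assessment is intended, the text should say so.

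Four stronger readings are tempting, and the documents do not support them.

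- *The rule contradicts the ITT plan.* It does not, formally: anyone with an assessment is analysed, and the blood-value rule applies to both arms. What suffers is the aim of ITT, because the result then rests on missing-at-random.
- *It uses up the drop-out allowance and breaks the power claim.* At the documents' own rate the loss is 8.6% overall. With one drop-out in 84 added, 52.4 datasets remain and power is 80.7%. Power of 75% to 77% needs an assumed further 10% loss in both arms, and the lower end also needs the extension to 12 weeks.
- *The bias can be sized.* That needs the share of benefit that withdrawn participants retain at week 13, which no section gives. Any figure would only return the assumption.
- *The loss falls wholly on EPO.* This is plausible, but there is no placebo rate, no reticulocyte-triggered rate and no statement that the earlier trial used the same thrombocyte limit. The 17% comes from patients, not relatives.

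The sentence on excluding patients who need a medication change may describe entry to the trial, so it cannot be counted as a second source of loss.

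**Conclusion.** The point stands in this limited form. Followed as written, the rule would cost about 5 of 29 EPO participants per sub-study their week-13 primary outcome, where the plan allows 3 per arm. The main harm is unequal, treatment-linked missing data; loss of power is secondary. The figure assumes that the earlier 17% carries over to a 12-week course, to this trial's limits and to both populations, with no placebo cases. The sampling interval alone runs from about 2 to 10 participants. The direction and size of any bias cannot be derived from the document. The concern itself does not depend on the exact rate: the article describes both the event and the earlier practice of continuing assessment, and now prescribes something else without explanation.

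**What to change.** Leave all blood-value limits and treatment-stopping criteria untouched. Reconcile Study design and procedures with the analysis, sample size and safety sections as follows:

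- Separate stopping study medication from withdrawal from outcome assessment.
- Keep the week-13 and six-month outcome assessments for participants who consent to them, and analyse them in their randomised arm.
- Count only true loss of outcome data as drop-out. The stated 58 recruits, 52 complete datasets and at least 80% power then stand.

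Separately, reconcile Participants, Limitations and Ethical considerations on whether a medication change after randomisation removes a patient from the study, or whether the exclusion applies only at entry.

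The cost is an amendment to the wording and a few off-treatment visits already planned for each participant. The estimated effect may be slightly diluted, because it then includes people who stopped early. Raising recruitment instead would be a poorer remedy: with 10% other loss, 52 / (0.9 × (1 − 0.171/2)) = 63.2, so about 64 per sub-study, and the imbalance in missing data would remain.
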